# FACILITY: feeding the family—the intergenerational approach to fight obesity, a cross-sectional study protocol

**DOI:** 10.3389/fped.2025.1450324

**Published:** 2025-03-31

**Keywords:** paediatric obesity, healthy lifestyle, risk factors, mothers, environment, low socioeconomic status

## Abstract

**Introduction:**

Paediatric obesity has been described by the World Health Organization as one of the most serious health challenges of the 21st century. Over the past four decades, the number of children and adolescents with obesity has increased between 10 and 12-fold worldwide.

**Methods:**

Childhood obesity is a complex and multifactorial outcome which can be attributed to factors such as socioeconomic status, ethnicity, lifestyle and eating habits. Beside personal-children-related factors, maternal (education, food knowledge, income) and environmental ones (food environment's features and accessibility) have been proven but their influences are still worth discussion. The cross-sectional study of the “FACILITY: feeding the family—the intergenerational approach to fight obesity” project aims at estimating children prevalence of overweight and obesity and assessing the impacts of lifestyle and of socio-economic-cultural and environmental factors on overweight and obesity.

**Results:**

Due to the current importance of developing multidisciplinary mother-child centred prevention programs, FACILITY cross-sectional study will investigate maternal and child socio-cultural, economic, environmental, health and lifestyle-related risk factors for the development of obesity.

**Discussion:**

The knowledge gained will provide the basis to develop a “primordial prevention program” to early tackle childhood obesity.

**Clinical Trial Registration:**

ClinicalTrials.gov, identifier (NCT06179381).

## Introduction

1

The Global Strategy for Women's, Children's, and Adolescents' Health (2016–2030) (1) plays a central role in the objective 3, Health and Well-being of the Agenda for Sustainable Development (2) for a future world in which every woman, child, and adolescent realises their rights to physical and mental health and well-being, in every setting (3). Obesity is defined as abnormal or excessive fat accumulation that poses a risk to health, due to an energy imbalance between energy intake and energy expenditure (4, 5). The reasons for this imbalance are complex and multifactorial (6). Health and nutritional status, lifestyle habits, biological features, environmental and socio-economic factors are nested within the family context, which in turn is nested within the community and the wider socio-geographical and cultural background (7).

Paediatric obesity has been described by the World Health Organization (WHO) as one of the most serious public health challenges of the 21st century (8). Over the past four decades, the number of children and adolescents with obesity has increased between 10 and 12-fold worldwide (9–11), with a rising prevalence among socially disadvantaged groups from low socio-economic backgrounds (11–13). In Italy, the prevalence of overweight and obesity for children aged 6–9 years is 29.8%, with the percentage of overweight and obesity around 20.4% and 9.4%, respectively (4).

Obesity prevention is recognized as the most feasible option for curbing the paediatric obesity epidemic (14). Most childhood obesity prevention programs have focused on school-aged children and have not proven so far to be effective in reversing the rising rates of childhood obesity (7). Indeed, by primary school entry, about 1 in 5 school-aged children were affected by obesity (15), suggesting that a prime opportunity to prevent childhood obesity has been missed (7). Thus, the prevention program should start very early, during and even before pregnancy and be shaped on mother-child dyads (16).

Maternal health is critical for healthy child growth and development (17). Indeed, maternal factors [i.e., Body Mass Index (BMI)], combined with an unhealthy family background (i.e., unhealthy eating habits and sedentary behaviour), strongly determine the lifestyle and nutrition behaviour of the child, predisposing him/her to the development of overweight or obesity (7, 18–20).

Along with the previously mentioned factors, socio-economic status (SES) has also been identified as a determinant for later obesity (11). Indeed, children with lower SES families have a steeper weight gain trajectory from birth with higher risk of obesity in adulthood (12, 21). Furthermore, children in poverty are more likely to become adults with lower SES and less wealth to pass on to future generations, in a vicious cycle, clearly acknowledging that obesity is increasingly related to poverty and is likely to be passed onto subsequent generations (22). Moreover, factors related to the socio-spatial environment play a key role in obesity (16, 23–25). For instance, the lack of healthy food availability, affordability and accessibility (e.g., food desert) has been positively linked to obesity. High neighbourhood walkability has been found to be associated with decreased prevalence of overweight and obesity, as well as the proximity to recreational facilities, parks, playgrounds, etc. have all been reported to be facilitators of physical activity (22, 26).

The overall aim of the FACILITY (feeding the aamily—the intergenerational approach to fight obesity) project is to identify determinants for early onset of childhood obesity considering both maternal and children risk factors in a sample of mother-child dyads attending a paediatric outpatient clinic of the Buzzi Children's Hospital in Milan, Italy. More in detail, the cross-sectional study aims at (i) estimating the prevalence of overweight and obesity in the target population, thus, providing updated estimates in the Milan area, a useful data for the planning of public health interventions; (ii) assessing the impacts of lifestyle and of socio-economic-cultural and environmental factors on overweight and obesity (Figure 1).

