### Study setting

2.1

To address FACILITY's purposes, 269 mother-child dyads will be consecutively enrolled at the paediatric outpatient clinic of the Buzzi Children's Hospital in Milan, Italy. The enrollment will last from February 2024 until December 2025.

Eligible dyads according to the following inclusion and exclusion criteria will be involved in the study.
-Inclusion criteria:
-For mothers: (i) age ≥18 years old, (ii) admission to the Department of Paediatrics, Buzzi Children's Hospital, (iii) ability to sign the informed consent.-For children/adolescents: (i) age between 2 and 18 years old, (ii) admission to the Department of Paediatrics, Buzzi Children's Hospital, (iii) informed consent signed by parents/local guardians.-Exclusion criteria:
-For mothers: (i) inability to understand the Italian and English language, (ii) refusal to sign the informed consent.-For children/adolescents: (i) presence of endocrine disorders (i.e., hypothyroidism, hypercortisolism, growth hormone deficiency), central nervous system damage (i.e., hypothalamic-pituitary damage because of surgery or trauma), genetic diseases either monogenic (i.e., leptin deficiency, MC4R mutation) or pleiotropic genetic syndromes (Prader-Willi, Bardet-Biedl), (ii) informed consent not written and signed by parents/local guardians.Moreover, if mothers return to the paediatric outpatient clinic with another child, the latter will also be enrolled if the inclusion criteria of the study are met. Written informed consent will be obtained from the parent or legal guardians. Variables will be collected by a trained research team (clinicians, registered dietitians, paediatricians, biologists).

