### Data analysis

2.4

In the cross-sectional study, sample size has been determined considering a prevalence of overweight and obesity in the target population of 17% and 4%, respectively (55). Considering a 95% level of confidence and 5% precision, 217 individuals for overweight and 52 for obesity prevalence estimates are required, for a total sample size of 269 mother-child dyads.

Enrolled subjects will be described with reference to all the collected variables by means of standard descriptive statistics. Prevalence of overweight and obesity will be estimated along with 95% confidence intervals. In order to assess the impacts of lifestyle and socio-economic, cultural, and environmental factors on overweight and obesity, logistic regression will be adopted. Overweight and obesity in children, as binary variables, will be the response in two separate logistic models, where socio-economic, cultural, and environmental factors, among all collected data, will be the independent variables. Indeed, performing different analyses according to the BMI status (overweight/obesity) will capture different health correlations, since the greater severity of overweight and obesity usually corresponds to an unhealthy lifestyle, and to a low SES (12, 21). Analyses will also be adjusted for potential confounders like age, sex or any other variable identifiable as such among the collected data.

Furthermore, if sample size allows, subgroups analysis by ethnicity (Caucasian or non-Caucasian) will be performed since it likely results in different cultural habits, impacting nutrition and other lifestyle factors (56, 57).

Missing data will be handled with multiple imputation.

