
Nevertheless, the cross-sectional phase of the FACILITY project has few limitations. First, due to the observational study design of the two study phases, a direct cause-and-effect relationship between the examined variables and overweight, obesity, and EAR can not be ascribed. Second, FACILITY focuses on mother-child dyads, excluding fathers from the analysis, although several evidence is highlighting the role of the triads for the child's development into adulthood (74, 75). Third, due to the specificity of the setting (single outpatient clinic in a North-Italian hospital), the results obtained from this study will not be generalizable to the entire Italian population. While children attending the outpatient clinic may have different health conditions and socio-economic backgrounds, it should be noted that visits are offered free of charge, which limits the participation of families with higher incomes who might prefer private healthcare settings, potentially leading to the underrepresentation of these groups. Moreover, the study will be conducted at a specific clinic, which may not reflect the diversity of healthcare settings across different regions of Italy, thus reducing the generalizability of the results to the national level.

Besides, the sampling frame may introduce a bias due to the non-random method of participant selection. Since children will be consecutively enrolled at the outpatient clinic, the sample may not be fully representative of the broader pediatric population. The recruitment method could result in a non-homogeneous distribution of age groups, as some age ranges may be more likely to attend the clinic due to specific health concerns.

Fourth, some of the outcome measures rely on parental reports and the use of structured interviews may lead to interviewer bias. Whenever possible, the authors have selected validated questionnaires, however, to date no validated tools to capture the mother's diet and her cultural influences exist. Therefore, structured interviews have been developed by the research team, which may mean that real lifestyle habits of the mothers and children would not be properly assessed due to the lack of validation of the interviews. Fifth, the authors recognize the lack of evaluation of additional potentially interesting variables correlated to childhood obesity (e.g., body composition, metabolic syndrome, food insecurity, screen time during mealtimes, family meals or shared meals).

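### Aim (i) promises prevalence estimates for the Milan area, but the sample is consecutive attenders at one hospital clinic and the article's own limitations do not support that reach

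*Protocol article*

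**What the plan says.** The Introduction describes the project's sample as mother-child dyads attending one paediatric outpatient clinic in Milan. It then gives aim (i) as estimating prevalence in a target population, "thus, providing updated estimates in the Milan area, a useful data for the planning of public health interventions". The step from clinic to area rests on the word *thus*.

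Section 2.1 (Study setting) fixes the sampling: "269 mother-child dyads will be consecutively enrolled at the paediatric outpatient clinic of the Buzzi Children's Hospital in Milan, Italy". The age criterion is "age between 2 and 18 years old". No population frame and no age quota are stated.

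Section 2.4 (Data analysis) says of aim (i): "Prevalence of overweight and obesity will be estimated along with 95% confidence intervals". It names no reference population. The sentence on age and sex, "Analyses will also be adjusted for potential confounders like age, sex or any other variable identifiable as such among the collected data", follows the logistic models and concerns confounding, so it serves aim (ii).

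The limitations in section 3 (Discussion) say that participants are not selected at random and that "the sample may not be fully representative of the broader pediatric population". They add that "The recruitment method could result in a non-homogeneous distribution of age groups", and that free-of-charge visits may leave higher-income families under-represented. The explicit statement that results will not generalise is made about Italy and the national level.

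**The concern.** A prevalence is only as meaningful as the population it refers to. Aim (i) offers the figure as a Milan-area estimate for public health planning, while the sampling supports a statement about eligible attenders at one clinic. Nothing in the stated analysis links the two, and the limitations point away from the link without narrowing the aim. After the limitations, the Discussion still offers updated data to Italian policymakers.

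The reach of the study's first result is at stake. The planned interval expresses sampling error only. A reader who takes the figure as a Milan prevalence would see an interval of about ±4.5 points and no sign that it also depends on who attends. The Introduction links lower socio-economic status to higher obesity risk, so on the article's own reasoning the income selection would tend to push the estimate up. The Italian benchmark in the Introduction (29.8% overweight and obesity combined) is for ages 6–9, so a figure pooled over ages 2–18 cannot be set beside it without age bands.

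**Working it through.** **1. The statements side by side.**

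| Question | What the article states | Section |
|---|---|---|
| Population claimed | Milan area, for public health planning | 1 Introduction |
| Population sampled | Consecutive attenders, one clinic, ages 2–18 | 2.1 Study setting |
| Link between them | None named; prevalence with 95% CI | 2.4 Data analysis |
| Own assessment | Non-random; may not represent the broader paediatric population; age mix could be uneven; higher incomes may be under-represented | 3 Discussion |
| Claim withdrawn? | For Italy, yes; for Milan, not explicitly | 3 Discussion |

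**2. Planned precision (inputs from section 2.4).** n = z²p(1−p)/d², with z = 1.96 and d = 0.05.

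- Overweight, p = 0.17: 3.8416 × 0.1411 / 0.0025 = 216.8, so 217 as stated.
- Obesity, p = 0.04: 3.8416 × 0.0384 / 0.0025 = 59.0, not the stated 52. That is a separate matter and nothing below depends on it.

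Half-width at n = 269: 1.96 × √(0.17 × 0.83 / 269) = 4.5 points for overweight, and 1.96 × √(0.04 × 0.96 / 269) = 2.3 points for obesity.

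**3. What an uneven age mix could do.** The article gives neither age-specific prevalence across 2–18 years nor the clinic's age distribution, so every input here is an assumption. The bands are 2–5, 6–10 and 11–17 years, with target shares 4/16, 5/16 and 7/16 (equal numbers per year of age). Each cell gives the crude prevalence in %, with crude minus standardised in points.

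| Assumed prevalence by band (%) | Standardised | Clinic mix 50/30/20 | Clinic mix 15/60/25 | Clinic mix 10/30/60 |
|---|---|---|---|---|
| 17 / 17 / 17 | 17.00 | 17.00 (0) | 17.00 (0) | 17.00 (0) |
| 13 / 20 / 17 | 16.94 | 15.90 (−1.04) | 18.20 (+1.26) | 17.50 (+0.56) |
| 10 / 25 / 17 | 17.75 | 15.90 (−1.85) | 20.75 (+3.00) | 18.70 (+0.95) |
| 8 / 30 / 20 | 20.13 | 17.00 (−3.13) | 24.20 (+4.07) | 21.80 (+1.67) |

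Example, last row: standardised 0.25 × 8 + 0.3125 × 30 + 0.4375 × 20 = 20.13; crude under the second mix 0.15 × 8 + 0.60 × 30 + 0.25 × 20 = 24.20.

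**4. Precision after standardising.** With target share w, clinic share m and prevalence p in each band, the variance is Σ w²p(1−p)/(269m). Over the twelve cells the half-width is 4.8 to 5.7 points, against 4.4 to 5.1 for the crude figure. It is wider in eleven cells. In the twelfth (last row, third mix) it is about equal, at 4.86 against 4.93.

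**5. What standardising cannot reach.** Suppose, again as an assumption, that overweight children are r times as likely to attend, whatever their age. A true 17% is then estimated as 0.17r / (0.17r + 0.83). For r = 1.25 this is 0.2125/1.0425 = 20.4%; for r = 1.5 it is 0.255/1.085 = 23.5%. The nominal 95% interval at n = 269 would cover 17% about 72% and 29% of the time. Age and sex weights do not correct this.

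**The case against.** The strongest reply is that the article already tells the reader all this. The sentence before the aims names the clinic, and the caveat about the broader paediatric population is not confined to Italy, so it naturally covers Milan. That stands in part: the weakness is disclosed, and the point is one of an aim left in conflict with its own caveats.

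Three further objections also stand, against stronger readings that a reader might infer:

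- **That a skewed age mix is expected.** The Discussion says only that recruitment could produce one.
- **That a single crude proportion over all ages is all that will be reported.** Section 2.4 names no estimator and rules out neither age bands nor standardisation. In a condensed article, with the full protocol and any analysis plan not shown, silence does not establish that these are absent.
- **That standardising by age and sex would rescue the Milan claim.** It leaves selection by income and by reason for attendance in place. A standardised figure could even look more like a Milan prevalence than it is.

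It is also fair that section 2.4 plans no comparison with population benchmarks, so misuse of the figure is a risk rather than a planned step. None of this removes the conflict, because no analysis plan would change the wording of aim (i).

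**Conclusion.** The point holds as a mismatch between the stated aim and the design. Aim (i) attributes the prevalence to the Milan area. The sampling supports a statement about eligible attenders at this clinic, and the limitations agree with the narrower reading without withdrawing the wider one.

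The size of any bias cannot be derived from the document. Under the assumed age patterns, the age-mix component runs from zero (prevalence flat by age) to about 4 points in either direction, more precisely −3.1 to +4.1. That compares with a half-width of about 4.5 points at n = 269 and 17%. A reader might infer that age-mix bias is known to match the planned precision. The documents do not support that, since it depends wholly on gradients and clinic mixes they do not give. The data stay usable; what changes is the population the first result may be said to describe.

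**What to change.** - Restate aim (i) as the prevalence of overweight and obesity among eligible children and adolescents attending this clinic, and drop the wording that presents it as an estimate for the Milan area.
- Report prevalence by age band, with 95% confidence intervals, beside the overall figure.
- If a Milan comparison is kept, add an estimate directly standardised by age and sex to the resident Milan population, next to the crude one. State with it that selection by income and by reason for attendance is not removed.

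The first two changes cost a sentence and one table; the age-band intervals will be wide because 269 children are split among them. The optional third needs public population counts and a few lines of analysis, and its interval will generally be somewhat wider (4.8 to 5.7 points under the assumptions above). No change to recruitment or sample size is needed.

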**Figure 1 F1:**
[figure not shown]
Graphical representation of FACILITY (feeding the family—the intergenerational approach to fight obesity) cross-sectional study. Understanding health and socio-economic-cultural maternal-child risk factors will enable the development of more effective public health policies for the prevention of childhood obesity to be drawn up in the future, according to the specific cultural and health needs of the target population.

## Methods and analysis

2

### Study setting

2.1

To address FACILITY's purposes, 269 mother-child dyads will be consecutively enrolled at the paediatric outpatient clinic of the Buzzi Children's Hospital in Milan, Italy. The enrollment will last from February 2024 until December 2025.

Eligible dyads according to the following inclusion and exclusion criteria will be involved in the study.
-Inclusion criteria:
-For mothers: (i) age ≥18 years old, (ii) admission to the Department of Paediatrics, Buzzi Children's Hospital, (iii) ability to sign the informed consent.-For children/adolescents: (i) age between 2 and 18 years old, (ii) admission to the Department of Paediatrics, Buzzi Children's Hospital, (iii) informed consent signed by parents/local guardians.-Exclusion criteria:
-For mothers: (i) inability to understand the Italian and English language, (ii) refusal to sign the informed consent.-For children/adolescents: (i) presence of endocrine disorders (i.e., hypothyroidism, hypercortisolism, growth hormone deficiency), central nervous system damage (i.e., hypothalamic-pituitary damage because of surgery or trauma), genetic diseases either monogenic (i.e., leptin deficiency, MC4R mutation) or pleiotropic genetic syndromes (Prader-Willi, Bardet-Biedl), (ii) informed consent not written and signed by parents/local guardians.Moreover, if mothers return to the paediatric outpatient clinic with another child, the latter will also be enrolled if the inclusion criteria of the study are met. Written informed consent will be obtained from the parent or legal guardians. Variables will be collected by a trained research team (clinicians, registered dietitians, paediatricians, biologists).

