#### Economic, social, cultural and environmental variables

Socio-economic and socio-cultural characteristics will be collected through structured interviews. Information on household income, job/work and housing status (surface; owned, rented, sub-rented, social housing, guest, other) will be collected to detect socio-economic status.

Family relationships will be derived from the Child-Parent relationship scale-Short Form (CPRS-SF), a 15-item questionnaire assessing mothers' perception of their relationship with their son or daughter (46, 47). The Personal Social Capital Scale (PSCS-8) short form will be used to assess maternal durable and trustworthy social connections (48). Maternal social participation will be investigated through a structured interview to explore type (i.e., religious, recreational, cultural and, political) and frequency of activities.

Environmental factors that may influence nutrition, physical activity and lifestyle will be considered through the collection of geo-data on the characteristics of the food environment (e.g., the built environment, proximity to recreational/sport facilities, parks) and the transport infrastructure (e.g., walkability) (35, 49).

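### Siblings can be enrolled under one mother, but the named analyses and sample size make no provision for within-family correlation; the effect is probably modest and falls mainly on family-level factors

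*Protocol article*

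**What the plan says.** The protocol article, section 2.1 (Study setting), states that "269 mother-child dyads will be consecutively enrolled at the paediatric outpatient clinic". It then adds that "if mothers return to the paediatric outpatient clinic with another child, the latter will also be enrolled", provided the child meets the inclusion criteria. Eligible children are aged 2 to 18, enrolment runs from February 2024 to December 2025, and no maximum number of children per mother is given.

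Section 2.4 (Data analysis) says that "Prevalence of overweight and obesity will be estimated along with 95% confidence intervals". For the risk factors, "Overweight and obesity in children, as binary variables, will be the response in two separate logistic models". The explanatory variables are to come from the social, economic, cultural and environmental data. Adjustment is for confounders such as age and sex, and missing data are multiply imputed. For the sample size, "Considering a 95% level of confidence and 5% precision, 217 individuals for overweight and 52 for obesity prevalence estimates are required".

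Many of the factors belong to the mother or the household. Table 1 records socio-economic status, social capital, social participation and the neighbourhood food environment for the mother only. The section on economic, social, cultural and environmental variables adds "Information on household income, job/work and housing status". Nowhere does the article mention a family cluster, GEE, a random effect, a robust variance or a restriction to one child per mother.

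**The concern.** Two children of one mother are not two independent records. They share nearly all the exposures that section 2.4 makes the independent variables, and their weight status is likely to be positively correlated. The article's own introduction argues that maternal and family background strongly shape a child's risk. When both the outcome and the covariate are alike within a family, a standard error that assumes independence counts the family's information more than once.

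At stake are the confidence intervals and p-values for the maternal, socio-economic and environmental factors named in the second aim, and to a lesser degree the width of the prevalence intervals in the first. The planned 269 also carries less information than its count suggests. The obesity model is the most exposed, because few events are expected and one concordant sibling pair is a visible fraction of them.

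**Working it through.** **Inputs from the article.** n = 269 dyads (section 2.1). Anticipated prevalences of 17% for overweight and 4% for obesity, 95% confidence, 5-point precision, and stated sizes of 217 and 52 (section 2.4).

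**Inputs assumed, because the article gives neither.** The share f of mothers who bring two children, and the sibling correlation ρ of the binary outcome.

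**1. The plan's own figure.** With n = z²p(1−p)/d², z = 1.96 and d = 0.05:
- Overweight: 1.96² × 0.17 × 0.83 / 0.05² = 216.8, so 217. This matches and shows that no design effect was included.
- Obesity: 1.96² × 0.04 × 0.96 / 0.05² = 59.0, not 52. This is a separate matter and does not affect the present point.

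**2. Design effect.** DEFF = 1 + (Σm²/Σm − 1)ρ, where m is the number of children per mother. With a share f bringing two and the rest one, Σm²/Σm = (1 + 3f)/(1 + f). The bracket equals the share of children who are in sibling pairs. The formula applies to a prevalence and, approximately, to the coefficient of a covariate that siblings share.

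**3. Consequences at n = 269.** Type I error = 2[1 − Φ(1.96/√DEFF)]. Half-width for 17% = 1.96 × √(0.17 × 0.83 × DEFF / 269). With DEFF = 1 the half-width is 4.49 points.

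| Mothers with two children | Children in pairs | ρ | DEFF | Type I error, mother-level factor | Half-width, overweight (points) |
|---|---|---|---|---|---|
| 2.6% | 5% | 0.2 | 1.01 | 5.1% | 4.51 |
| 10% | 18% | 0.3 | 1.05 | 5.6% | 4.61 |
| 20% | 33% | 0.3 | 1.10 | 6.2% | 4.71 |
| 20% | 33% | 0.5 | 1.17 | 7.0% | 4.85 |
| 30% | 46% | 0.5 | 1.23 | 7.7% | 4.98 |

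Worked line for 20% and 0.3: (1 + 0.6)/(1 + 0.2) = 1.333; DEFF = 1 + 0.333 × 0.3 = 1.10; 1.96/√1.10 = 1.869; type I error = 6.2%.

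**4. Where the precision target would fail.** The 5-point target holds while DEFF stays below 269/216.8 = 1.24. Every row satisfies this, the last one narrowly. For obesity at 4%, the half-width is 2.34 points with DEFF = 1 and 2.34 × √1.23 = 2.6 points in the last row.

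**5. Simulation check.** Settings: 269 children, prevalence 17%, binary sibling correlation about 0.36, a mother-level covariate with no effect, 2,000 runs, Monte Carlo error about 0.5 points.

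| Children in pairs | Ordinary logistic | Cluster-robust by mother |
|---|---|---|
| 0% | 5.7% | 5.7% |
| 10% | 4.6% | 4.8% |
| 30% | 6.4% | 5.7% |
| 50% | 6.7% | 5.5% |

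Inflation cannot be detected at 10% and is about one point at 30% to 50%. The cluster-robust errors remove most of it.

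**6. Obesity events.** 0.04 × 269 = 10.8, so about 11 cases. One pair of siblings who both have obesity supplies 2/10.8, about a fifth of the events.

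**The case against.** **Independence is implied, not stated.** The article names no variance estimator and no interval method, and a logistic model with cluster-robust errors is still a logistic model. A fuller analysis plan may contain the correction. This stands, and rules out saying that the authors chose to treat siblings as independent. It does not dispose of the point. The article itself sets the sibling rule, the model, the adjustment and the missing-data method, and its one reproducible calculation (217) assumes independence.

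**The assumed values are generous.** A sibling enters only if the mother returns within the enrolment window with another eligible child. If 20% of mothers do so, a third of all children are in pairs. Under a bivariate-normal liability model, a latent sibling correlation of 0.5 gives a binary correlation of only 0.28 at 17% prevalence and 0.19 at 4%. The shared covariates in the model would also absorb part of the correlation. This stands: the lower rows of the first table are closer to an upper bound than to an expectation.

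**No stated precision goal fails.** Correct for the range shown. The concern is mainly with the regression inference.

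**Two stronger readings are tempting.** A reader might infer that all standard errors are too small. For covariates that differ between siblings, such as age, sex, diet score, sleep or screen time, the direction can go either way. A reader might also infer that a returning mother is counted twice in the maternal descriptives. Section 2.4 says only that enrolled subjects will be described, and section 2.3 gives each participant a unique number. Nothing says that mothers are tabulated once per dyad.

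**Conclusion.** The point holds in a limited form. The design admits siblings by rule, and the analysis and sample size as written make no provision for their correlation. Followed literally, the plan would understate standard errors for the prevalences and for family-level covariates, which are the main exposures of the second aim.

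The size is uncertain and probably modest. It is negligible if few mothers return. At the top of the assumed range (30% of mothers with two children, correlation 0.5) the design effect is about 1.2 and type I error for mother-level factors stays below 8%. All of this rests on an assumed sibling share and correlation, at most two children per mother, and a variance that ignores families. It should be corrected because the remedy is nearly free, but it does not threaten the prevalence aim.

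**What to change.** - State that the logistic models and the prevalence intervals will use mother as the cluster, by GEE or cluster-robust standard errors on a mother identifier. Confirm that data capture links each child to the mother, and carry that identifier into the imputation.
- Add a sensitivity analysis restricted to the first-enrolled child of each mother. This matters most for obesity, where robust variances are themselves unreliable with about 11 events.
- Say whether 269 counts children or distinct mothers, report both numbers, and summarise each mother once in the maternal descriptives.

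The cost is slightly wider intervals for family-level factors, one option in the analysis code and a sentence or two in the plan. No extra data beyond the mother-child link are needed.
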